# Involuntary reflexive pelvic floor muscle training in addition to standard training versus standard training alone for women with stress urinary incontinence: study protocol for a randomized controlled trial

**DOI:** 10.1186/s13063-015-1051-0

**Published:** 2015-11-17

**Keywords:** Electromyography, Exercise, Muscle contraction, Pelvic floor, Reflex

## Abstract

**Background:**

Pelvic floor muscle training is effective and recommended as first-line therapy for female patients with stress urinary incontinence. However, standard pelvic floor physiotherapy concentrates on voluntary contractions even though the situations provoking stress urinary incontinence (for example, sneezing, coughing, running) require involuntary fast reflexive pelvic floor muscle contractions. Training procedures for involuntary reflexive muscle contractions are widely implemented in rehabilitation and sports but not yet in pelvic floor rehabilitation. Therefore, the research group developed a training protocol including standard physiotherapy and in addition focused on involuntary reflexive pelvic floor muscle contractions.

**Methods/design:**

The aim of the planned study is to compare this newly developed physiotherapy program (experimental group) and the standard physiotherapy program (control group) regarding their effect on stress urinary incontinence. The working hypothesis is that the experimental group focusing on involuntary reflexive muscle contractions will have a higher improvement of continence measured by the International Consultation on Incontinence Modular Questionnaire Urinary Incontinence (short form), and — regarding secondary and tertiary outcomes — higher pelvic floor muscle activity during stress urinary incontinence provoking activities, better pad-test results, higher quality of life scores (International Consultation on Incontinence Modular Questionnaire) and higher intravaginal muscle strength (digitally tested) from before to after the intervention phase. This study is designed as a prospective, triple-blinded (participant, investigator, outcome assessor), randomized controlled trial with two physiotherapy intervention groups with a 6-month follow-up including 48 stress urinary incontinent women per group. For both groups the intervention will last 16 weeks and will include 9 personal physiotherapy consultations and 78 short home training sessions (weeks 1–5 3x/week, 3x/day; weeks 6–16 3x/week, 1x/day). Thereafter both groups will continue with home training sessions (3x/week, 1x/day) until the 6-month follow-up.

To compare the primary outcome, International Consultation on Incontinence Modular Questionnaire (short form) between and within the two groups at ten time points (before intervention, physiotherapy sessions 2–9, after intervention) ANOVA models for longitudinal data will be applied.

**Discussion:**

This study closes a gap, as involuntary reflexive pelvic floor muscle training has not yet been included in stress urinary incontinence physiotherapy, and if shown successful could be implemented in clinical practice immediately.

**Trial registration:**

NCT02318251; 4 December 2014

First patient randomized: 11 March 2015

**Electronic supplementary material:**

The online version of this article (doi:10.1186/s13063-015-1051-0) contains supplementary material, which is available to authorized users.

## Background

Stress urinary incontinence (SUI), the most common urinary incontinence subtype in women with a prevalence of 24.8 % [1], is defined as involuntary loss of urine during effort or physical exertion (for example, during sporting activities) or upon sneezing or coughing [2]. Activities typically provoking SUI raise the intra-abdominal pressure and impact loading on the pelvic floor muscles (PFM) and require strong, rapid, and reflexive PFM contractions to maintain continence [3–6]. Fast and strong PFM contractions result in the generation of an adequate squeeze pressure in the proximal urethra, which maintains a pressure higher than that in the bladder, thus preventing leakage [7]. PFM function regarding power (rate of force development) is impaired in incontinent women compared to continent women [4, 6].

PFM training — defined as a program of repeated voluntary PFM contractions taught and supervised by a health care professional — is the most commonly used physiotherapy treatment for women with SUI, is effective with all types of female incontinence, and, therefore, is recommended as a first-line therapy [8, 9]. As endorsed by the International Consultation on Incontinence, PFM training should generally be the first step of treatment before surgery [10]. However, standard SUI physiotherapy concentrates on voluntary contractions even though the situations provoking SUI such as sneezing, coughing, jumping, and running [2] require involuntary fast reflexive PFM contractions [4]. Although training procedures following the concepts of training science and sports medicine are generally well known and widely implemented in rehabilitation and sports [11, 12], an optimal and well-standardized training protocol for involuntary, fast, and reflexive PFM contractions still remains unknown.

Consequently, the research group of the present study developed a standardized therapy program, which includes the standard physiotherapy and additionally focuses on involuntary fast reflexive PFM contractions. The additional exercises are well known and applied in physiotherapy, however not yet regarding SUI.

Therefore, the aim of the present study is to compare two different physiotherapy programs: standard training plus involuntary reflexive PFM training versus standard training alone, regarding their effect on SUI and the impact of incontinence symptoms on quality of life. Both programs include standard physiotherapy. Both follow the concepts of training science, that is, periodization/exercise sequence and training of specific muscle strength components [11, 12]. One program focuses on voluntary fast contractions (standard physiotherapy; control group); the other one additionally focuses on involuntary fast reflexive PFM contractions (experimental group). The secondary objective, based on secondary and tertiary outcomes, is a deeper insight into the functioning of the PFM (PFM activity characteristics and muscle action forms) by evaluating their activity measured by electromyography (EMG) in the quality of life of patients with SUI and in patients’ therapy adherence.

## Methods/design

### Study design

The present study is a single-centered, prospective, triple-blinded (participant, investigator, outcome assessor), parallel group, non-inferiority randomized controlled trial with two physiotherapy intervention groups with a 6-month follow-up.

### Blinding

Participants will be blinded against the type of received physiotherapy (control group, experimental group). The participant information document will not provide any information regarding the differences in the experimental and control therapy protocols in a way that women could find out about their group allocation. All investigators involved in data acquisition, data reduction, data analyses, and statistics will also be blinded against group allocation. The physiotherapists in charge of the therapy cannot be blinded against group allocation and therefore will not be involved in data acquisition, data reduction, data analyses, or statistics.

### Participants

With ethics committee approval (Ethics Committee of the Canton of Bern reference number 249/14 on 12 November 2014; Chairperson [name]. [name]), which is in accordance with the Declaration of Helsinki and the Swiss Human Research Act, and written informed consent, patients will be included on the condition that they are female adults aged 18–70 years, suffer from SUI (based on the patient’s history) or mixed urinary incontinence (with dominant SUI), are one year post-partal, parous, nulliparous, pre- or post-menopausal, have a BMI of 18–30 kg/m^2^, are medically and physically fit for the measurement and therapeutic exercises (running, jumps), and, in case of systemic or local estrogen treatment, stable for the past 3 months prior to inclusion.

Exclusion criteria are: urge incontinence or predominant urgency in incontinence; prolapse > grade 1 POP-Q [13] (uterus, cystocele, rectocele during Valsalva maneuver); pregnancy (urine test to accomplish); current urinary tract or vaginal infection, menstruation on the day of examination; lactation period not yet finished; contraindications for measurements or interventions, for example, acute inflammatory or infectious disease, tumor, fracture; de novo systemic or local estrogen treatment (<3 months); de novo drug treatment with anticholinergics or other bladder active substances (tricyclic antidepressants, selective serotonin reuptake inhibitors). Interventions and measurements would be individually modified in case of temporary loss of physical fitness for certain exercises.

### Outcomes

#### Primary outcome measure

The primary outcome measure will be the International Consultation on Incontinence Modular Questionnaire Urinary Incontinence short form (ICIQ-UIsf), which provides a brief and robust assessment of the impact of symptoms of urinary incontinence on quality of life and outcome of treatment and is scored on a scale from 0 (not) – 21 (severely affected). Previous research has examined the ICIQ-UIsf questionnaire and found it to have good reliability and constructive validity [14] and to correlate well with urodynamic findings [15]. This questionnaire is validated in the German language [16]. For measurement time points see Table 1.

**Table 1 Tab1:** Outcome measures and personal physiotherapy consultation time points

	Baseline before intervention phase	16-week intervention phase (1) after randomization into control group and experimental group									After intervention phase	6-month follow-up
Visits	1	2	3	4	5	6	7	8	9	10	11	12
Weeks	−1	1	2	4	6	8	10	12	14	16	16 + 1	16 + 26
Personal Physiotherapy Consultation (PT)		PT1	PT2	PT3	PT4	PT5	PT6	PT7	PT8	PT9		
Primary outcome												
ICIO-UIsf	x		x	x	x	x	x	x	x	x	x	
Secondary outcomes												
EMG (rest, MVC)	x										x	x
EMG (VFC, SJ, CMJ, DJ)	x										x	x
EMG (running 7, 9, 11 km/h)	x										x	x
ICIQ-UIsf												x
ICIQ-LUTSqol	x										x	x
20-min pad test	x										x	x
Tertiary outcomes												
Manual muscle testing	x										x	x
Therapy adherence			x	x	x	x	x	x	x	x	x	x

*ICIQ-UIsf* International Consultation on Incontinence Modular Questionnaire Urinary Incontinence (short form), *EMG* electromyography, *MVC* maximal voluntary contraction, *VFC* voluntary fast contraction, *SJ* squat jump, *CMJ* counter movement jump, *DJ* drop jump, *ICIQ-LUTSqol* International Consultation on Incontinence Modular Questionnaire Urinary Incontinence Symptoms Quality of Life

#### Secondary and tertiary outcome measures

The secondary outcome measure will be the EMG activity of the PFM during rest, maximal voluntary contractions (MVCs), voluntary fast contractions (VFCs), and during involuntary contractions during squat jumps (SJs), counter movement jumps (CMJs), drop jumps (DJs), and treadmill running at 7, 9, and 11 km/h [17]. As there is a relation between high impact activities and SUI prevalence [18], those different and comprehensive test exercises will be chosen to represent typical situations of involuntary urine loss and different muscle action forms (isometric-concentric voluntary muscle actions: MVC, VFC; involuntary eccentric-concentric muscle actions: SJ, CMJ, DJ, running).

Additionally, the 20-min pad test [19, 20] and the International Consultation on Incontinence Modular Questionnaire Urinary Incontinence Symptoms Quality of Life (ICIQ-LUTSqol) [21] will be implemented as secondary outcomes. The pad test will provide information regarding the efficacy of the therapy protocols to the UI symptoms (such as changes in the leakage volume) and the ICIQ-LUTSqol evaluates the impact on the participant’s quality of life with reference to social effects. It consists of 20 questions, which lead to a summary score between 19 and 76 points (greater values indicate higher impact on quality of life) and is available in German [22].

As tertiary outcomes PFM strength will be digitally assessed according to the Oxford Grading Scale [23], and adherence to the home exercise program will be assessed, that is, how many of the total therapy sessions will be completed individually. The home exercise adherence data will be collected with a simple training diary questionnaire.

For measurement time points, see Table 1.

### EMG procedure, instrumentation, and data reduction

#### Instrumentation

A vaginal surface EMG probe (3-pol-STIMPON® electrode (Innocept Biobedded Medizintechnik GmbH, Gladbeck, Germany) in a differential configuration will be used to measure PFM activity. The STIMPON electrode is a certified device (patent number EP 0 963 217 B1, CE 0482) which is widely applied in pelvic floor rehabilitation. The probe is made of polypropylene and with this soft surface therefore optimally designed to adapt its form to individual vaginal cavities and not to slip out of position during impact loads. The single reference adhesive surface electrode (Ambu Blue Sensor N, Ballerup, Denmark) will be fixed on the right iliac crest.

Running will be conducted on a Kettler Marathon TX1 treadmill device (Ense-Parsit, Germany) at speeds of 7, 9, and 11 km/h and 1° inclination. For the DJ a 20-cm step will be used.

To detect events necessary for the parameterization of the time-dependent signals such as heel strike (= initial contact = time point zero (T0)) during running, two load cells (Type KMB52 K 10KN, Megatron, Putzbrunn, Germany) are attached under the treadmill. T0 of SJ, CMJ, and DJ will be identified by using a force plate (Type 9286BA, Kistler Winterthur, Switzerland). Electrodes will be connected to the transmitter by short wire and the signals will be sent wirelessly to the receiver (TeleMyo 2400 G2, Noraxon European Service Center, Cologne, Germany).

#### EMG measurement procedures

The subjects will be instructed in the vaginal insertion of the surface EMG probe using ultrasound lubrication and will perform the insertion themselves after emptying their bladder. They will wear a loose running suit and running shoes of the same type but individual size. PFM EMG will be measured for 30 seconds (s) without any voluntary contraction and twice for 5 s during MVC (contraction maximal as possible), which will be instructed and controlled by intravaginal manual muscle testing before the EMG measurements, and ten times for VFC in a standing position, with a 15-s break between the single measurements. After that they will perform five SJs, five CMJs, and five DJs, again with 15 s between the single measurements, each jump being demonstrated and practiced before EMG recordings. Thereafter, the subjects will perform a warm-up of treadmill walking (5 km/h) for 30 s, then running at 7, 9, and 11 km/h consecutively until they reach a steady state. As soon as they reach the steady state at the respective speed, the data acquisition will be started: all data will be measured continuously for 10 s and the first ten step cycles of the right leg will be analyzed. Between the measurements of the different speeds the treadmill will be stopped, followed by a 1-minute break until the same procedure is restarted with the next speed [17].

#### Data reduction

All signals will be sampled at a rate of 3 kHz (sampling interval (dt) equals 0.333 ms) using a measurement amplifier and 1-bit analog-to-digital converter (ME-2600i, SisNova Engineering, Zug, Switzerland) and the software package “Analoge und digitale Signalverarbeitung” (ADS) version 1.12 (uk-labs, Kempen, Germany).

The EMG signals will firstly be first order high-pass filtered with a cut-off frequency of 10 Hz by EMG preamplifier leads to reject or eliminate artifacts and later digitally low-pass filtered by Noraxon Receiver Hardware with a cut-off frequency of 500 Hz. Secondly, to identify amplitude peaks during MVC, EMG will be calculated as RMS (200 ms moving window). 100 % of EMG equals the average of the two peak amplitude values during the two 5-s sessions of MVC. Thirdly, EMG variables of pre-activity and reflexivity will be calculated as RMS values within 30-ms intervals [24–26], averaged over 10 steps, and normalized to peak MVC (% EMG). The variables of pre-activity and reflexivity (30-ms intervals) will follow former study protocol intervals [17, 24, 25]. All variables will be analyzed using the software package MATLAB (MathWorks, Natick, MA, USA). Outcomes will be averaged over the repetitions of each exercise.

### Statistical methods

#### Hypothesis

Alternative hypothesis for primary outcome: It is hypothezised that the experimental group focusing on involuntary pelvic floor muscle contractions will have a statistically higher improvement of continence measured by ICIQ-UIsf questionnaire from before to after the intervention phase.

#### Sample size calculation

Sample size calculation was performed with G*Power software [27], using the statistical model of an ANOVA approach (repeated measures, within-between interactions). To this day there is no comparable training study (RCT) to estimate sample size based on available data from ICIQ-UIsf. Consequently, sample size was estimated theoretically and an effect size of = 0.1, indicating a small effect [28] will be accepted. The sample size was calculated for the primary outcome ICIQ-UIsf with the following assumptions: α = 0.05, power (1–β error probability) = 0.8, number of groups = 2, number of measurements = 10; correlations among repeated measures were estimated conservatively low with 0.5. Based on these assumptions, a total sample size of N = 80 was estimated. In anticipation of dropouts (10 %: n = 8) or a violation of normality assumption (+10 %: +n = 8), a final sample size of N = 96 (48 participants per group) results.

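### The 80% power claimed for a small effect belongs to a ten-visit interaction under sphericity; for the before-to-after hypothesis the detectable difference is about 0.6 SD

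*Protocol article*

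**What the plan says.** The Sample size calculation section of the protocol article uses a repeated-measures ANOVA for the within-between interaction. Its inputs are "α = 0.05, power (1–β error probability) = 0.8, number of groups = 2, number of measurements = 10", and it adds that "correlations among repeated measures were estimated conservatively low with 0.5". The effect is described thus: "an effect size of = 0.1, indicating a small effect [28] will be accepted". The symbol is lost in the text; it is taken here as Cohen's f. From these inputs "a total sample size of N = 80 was estimated". Eight women are added for dropout and eight for possible non-normality, giving 96. No nonsphericity correction is stated, and the effect is not expressed in SD units or ICIQ-UIsf points.

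The Hypothesis section states the primary hypothesis as greater improvement in the experimental arm "from before to after the intervention phase". The Statistical analyses section plans the primary comparison as a longitudinal ANOVA over ten time points, with last observation carried forward. Table 1 places the ten primary-outcome questionnaires at weeks −1, 2, 4, 6, 8, 10, 12, 14, 16 and 17.

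**The concern.** With two groups compared once, f is half the standardised difference, so f = 0.1 reads naturally as 0.2 SD. In a ten-visit interaction the same number means something else: it describes how much the difference between arms varies over the visits, and the repeated visits add to the information. A reader who takes the sentence at face value will believe that the trial can detect a small benefit in before-to-after change, and may read a null result as excluding one.

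The stated power also needs sphericity. With questionnaires 1 to 3 weeks apart over 18 weeks, neighbouring scores are likely to correlate more strongly than distant ones. Epsilon then falls below 1, and power falls with it.

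**Working it through.** **Inputs.** From Sample size calculation: f = 0.1, alpha 0.05, k = 2 groups, m = 10 measurements, rho = 0.5, N = 80, final N = 96, 8 dropouts (so 88 remain). From Table 1: the visit weeks. Assumed here: epsilon values below 1, and the time courses.

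**1. Reproducing N = 80.** For the interaction, λ = f²·N·m·ε/(1 − rho), df1 = (k − 1)(m − 1)ε and df2 = (N − k)(m − 1)ε. With ε = 1 and N = 80, λ = 0.01 × 80 × 10/0.5 = 16 on F(9, 702), and power is 0.805. N = 78 gives 0.792, so 80 is the smallest even total that reaches 0.80. Two other definitions of λ, f²·df2 and f²·N·(m − 1), would need 178 and 176. So ε = 1 with the formula above is inferred from the match.

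**2. What f = 0.1 means over ten visits.** Let d_t be the difference between arms at visit t, in outcome SDs. Then f² = var(d_t)/4, so f = 0.1 means SD(d_t) = 0.2. If d_t has the shape D·s_t, with s running from 0 at baseline to 1 after treatment, then D = 0.2/SD(s). With rho = 0.5 the SD of a change score is √(2 × 0.5) = 1 outcome SD, so D is also the standardised difference in change. The last two columns give the power of a t test on change scores (two-sided 0.05).

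| Time course | SD(s) | D | N = 80 | N = 96 |
|---|---|---|---|---|
| Linear over visits | 0.319 | 0.63 | 0.79 | 0.86 |
| Full effect straight after baseline | 0.300 | 0.67 | 0.84 | 0.90 |
| Ramp starting after week 9 | 0.376 | 0.53 | 0.65 | 0.73 |
| Step at mid-course | 0.500 | 0.40 | 0.42 | 0.49 |

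Using the actual weeks in place of visit number also gives 0.63 SD for the linear course. If the difference stays between zero and its final value, SD(s) cannot exceed 0.5, so D cannot be below 0.40. An artificial course (half the effect at once, the rest only at the last visit) would give 0.89.

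**3. Power for a difference that is small.** For 0.2 SD in change, the non-centrality of the t test is 0.2 × √(N/4). Power is 0.14 at N = 80, 0.15 at N = 88 and 0.16 at N = 96. The ten-visit test does no better: 0.2 SD reached linearly is f = 0.2 × 0.319/2 = 0.032, λ = 0.032² × 1600 ≈ 1.6 at N = 80, and power is about 0.11.

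**4. Sphericity.** Ten-visit interaction, f = 0.1, rho = 0.5:

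| ε (assumed) | N = 80 | N = 88 | N = 96 |
|---|---|---|---|
| 1 | 0.805 | 0.849 | 0.885 |
| 0.75 | 0.71 | 0.76 | 0.80 |
| 0.5 | 0.58 | 0.63 | 0.67 |

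**5. Detectable before-to-after difference, 80% power.** The normal approximation is (1.960 + 0.842) × √(4/N), which is 0.597 at N = 88 and 0.572 at N = 96. With the t distribution these become 0.60 and 0.58 SD. Adjusting for baseline multiplies by √(1 − 0.5²) = 0.866, so 0.604 × 0.866 = 0.52 SD at N = 88.

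**The case against.** The strongest reply is that the calculation matches the analysis. The sample size is for a ten-visit within-between interaction, the Statistical analyses section plans that test, and N = 80 reproduces to the patient. This stands: there is no arithmetic error. The Hypothesis wording could also be read as naming the period of improvement rather than a two-point contrast. Even so, the small-effect label misleads, because the ten-visit test has only about 11% power at N = 80 for a 0.2 SD difference reached linearly.

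A reader might infer something stronger: that the trial has only 42% power at N = 80, or 49% at N = 96, for its own hypothesis. The document does not support that as a consequence of its inputs. Those figures arise when f = 0.1 is re-applied with two measurements, which changes a stated input from ten to two and so powers a different effect, 0.40 SD in change. With the ten-visit effect kept and linear divergence, before-to-after power is 0.79 and 0.86. The lower pair is one scenario; a mid-course step gives the same numbers.

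On sphericity, it is fair to say that the protocol gives no correlation data, that a condensed article may omit a software setting, and that a true correlation above 0.5 would raise power. It would also overstate the case to say that 80% power holds only under perfect sphericity: that is true of N = 80, but with all 96 analysed it survives down to epsilon of about 0.75. What remains is that the power figure is published without the assumption that produces it, and the two 10% allowances were made for dropout and non-normality, not for this.

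**Conclusion.** The point holds as a misstatement of what the trial can detect, not as a computing error. The 80% at N = 80 is correct for the planned ten-visit interaction if epsilon is 1. Calling the underlying effect small is not correct for the before-to-after hypothesis: it corresponds to about 0.63 SD under linear divergence, and it cannot be under 0.40 SD unless the difference at some visit overshoots its final value or reverses sign. At the final size the trial has 80% power for roughly 0.6 SD in change, and about 15% for 0.2 SD. For the planned test at 88 to 96 analysed, power is 0.76 to 0.80 at epsilon 0.75 and 0.63 to 0.67 at 0.5.

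These results rest on reading the effect size as Cohen's f, on the protocol's correlation of 0.5, on assumed time courses, and on epsilon values that the document neither gives nor excludes.

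**What to change.** Keep 96 randomised and revise the Sample size calculation text:

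- Remove the description of the effect as small.
- State that N = 80 refers to the ten-visit interaction with epsilon = 1, and show power for lower values, for example 0.5 to 0.75.
- State the detectable difference for the contrast in the Hypothesis section: about 0.60 SD in change score with 88 analysed (96 less the 8 planned dropouts), or 0.58 SD with all 96, at 80% power, two-sided 0.05, correlation 0.5.
- Quote a baseline-adjusted figure (about 0.52 SD with 88) only if that contrast is made the primary test. Otherwise the stated power would again belong to a test that is not the planned one.

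The cost is wording. The stated detectable effect becomes less favourable, and no extra patients are needed.
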